## Methods/Design

### Study design

Telerehab III is a multi-center, prospective, randomized, controlled clinical trial recruiting one hundred and forty stable coronary artery disease (CAD) and/or chronic heart failure (CHF) patients (Fig. 1). Patients are randomized in equal proportions to one of two groups: internet-based telerehabilitation in addition to center-based rehabilitation (intervention group) or center-based rehabilitation alone (control group). Patients are enrolled after completion of the first six weeks of their phase II center-based rehabilitation program. They are followed for a minimum of 6 months and a maximum of 25 months.

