### Study population

Patients belonging to one of the two cardiac disease categories (ia CAD for which patients were treated conservatively, with a percutaneous coronary intervention or with coronary artery bypass grafting OR ib CHF with reduced EF (NYHA I, II and III) OR ic CHF with preserved EF (NYHA I, II and III)) and who had signed the informed consent form; are eligible to participate. All patients were on optimal medical treatment and stable for >4 weeks. In addition, eligible patients are at least 18 years and maximally 80 years old. They must have a personal computer with internet connection.

The main exclusion criteria are: the presence of a pre-existing non-cardiovascular condition (orthopedic and/or neurological), limiting the patient’s ability to actively engage in exercise training; the presence of terminal disease, dementia and cognitive impairment that unables the patient to use the telerehabilitation equipment or appear to follow-up visits. The complete list of inclusion and exclusion criteria is provided in Table 2.

**Table 2 Tab2:** Summary of key inclusion and exclusion criteria for Telerehab III

Inclusion criteria
ia. CAD patients treated conservatively, with PCI or CABG.
ib. CHF patients with reduced EF
ic. CHF patients with preserved EF
ii. Current active rehabilitation on one of the recruiting centres
iii. Possesion of personal computer with internet connection
iv. Age >18 and <80 years
v. Familial with Dutch language
vi. Informed consent
Exclusion criteria
i. Orthopaedic and/or neurological condition, limiting the patient’s ability to actively engage in exercise training sessions
ii. Impairment to use the telerehabilitation equipment or appear at follow-up visits (terminal disease, dementia and cognitive impairment)
iii. Simultaneous participation in anoter clinical trial
iv. Patients with CHF NYHA IV
v. Patients with a history of VF. exertional sustained VT/supraventricular tachycardia within the previous 6 months

*CAD* coronary artery disease, *CHF* chronic heart failure, *PCI* percutaneous coronary intervention, *CABG* coronary artery bypass grafting, *EF* ejection fraction, *NYHA* New York Heart Association, *VF* ventricular fibrillation, *VT* ventricular tachycardia

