### Sample size

The sample size calculation is based on a 20 % effect size of VO2 peak , which is comparable to the effect reported by Frederix et al. in their Telereab II study [9]. In order to attain a minimal power of 95 %, at an alpha error probability < 0,05; 140 patients should be recruited when taking into account a dropout rate of 30 % during follow-up.

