### Randomization

Patients are assigned to one of two treatment arms by a central computerized randomization system. Block randomization is used to ascertain equal distribution of patients in the intervention and control group in the different recruiting hospitals. In order to achieve a balance of relevant patient characteristics in both study arms, it will be assessed whether patients are matched for age, gender, cardiac disease category and cardiovascular risk factor profile. When intervention and control patients are not matched for these characteristics, a second randomization process will be done to ascertain matching. Investigators are unaware of the randomization sequence.

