### Statistical analysis

The statistical analysis will be performed according to the Intention-to-treat principle. For continuous data, the Shapiro-Wilk test will investigate whether normal distribution is present. When data are not normally distributed, the Mann–Whitney U-test will be used for the comparison between groups; and the Wilcoxon Signed Rank test will be used for the comparison within groups. When data are normally distributed the One Way ANOVA repeated measures test will be used for both between and within group analysis. Kaplan-Meier plots and log-rank tests will be used to compare censored time-to-event data; for the time to first cardiovascular rehospitalization and time to first rehospitalization for any reason. The statistical software package SPSS will be used for analysis. P-values <0,05 will be considered statistically significant.

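### The fixed tests use none of the characteristics the protocol wants balanced (disease category, age, gender); they are valid on average but less efficient than a stratified or adjusted analysis

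*Protocol article*

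**What the plan says.** The Study design section enrols "one hundred and forty stable coronary artery disease (CAD) and/or chronic heart failure (CHF) patients", and "Patients are randomized in equal proportions to one of two groups". The Study population section shows how wide the mix is: it runs from conservatively treated coronary disease to "CHF with reduced EF (NYHA I, II and III") and heart failure with preserved ejection fraction in the same classes.

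The Randomization section describes blocks within hospitals. It then says that it will be assessed "whether patients are matched for age, gender, cardiac disease category and cardiovascular risk factor profile". If the arms do not match, a second randomization is planned. Disease category, age and gender are not randomization strata.

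The Statistical analysis section fixes the tests. For time to first cardiovascular or any rehospitalization, "Kaplan-Meier plots and log-rank tests will be used to compare censored time-to-event data". For continuous endpoints, a Shapiro-Wilk result decides between Mann-Whitney and repeated-measures ANOVA. No covariate or stratum is named. The Study endpoints section mentions adjustment for baseline for HeartQol, IPAQ and EQ-5D only.

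**The concern.** The protocol singles out certain characteristics as relevant enough to balance, and then leaves them out of every test it specifies. Heart failure and coronary disease without heart failure can be expected to differ in rehospitalization risk and in exercise capacity. Leaving out a prognostic factor costs precision, and a surplus of heart-failure patients in one arm of the realised trial is not corrected.

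This matters most for the rehospitalization endpoints. They have no baseline value of the outcome to adjust for, so disease category is the obvious collected variable to use. For VO2 peak, the baseline measurement already carries much of the same information.

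**Working it through.** **The plan's own figure.** The sample size section states "The sample size calculation is based on a 20 % effect size of VO2 peak", "In order to attain a minimal power of 95 %, at an alpha error probability < 0,05" and "140 patients should be recruited when taking into account a dropout rate of 30 % during follow-up". No standard deviation is given, so 140 cannot be derived from the text; it can only be inverted. Completers: 140 × 0.70 = 98, or 49 per arm. Taking a two-sided 5% level (the protocol does not state sidedness), the implied standardized difference is (1.960 + 1.645) × √(2/49) = 0.728. This is the reference effect for VO2 peak below.

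**1. How large is a chance imbalance?** Assume a heart-failure share q of 20% to 40% (not in the protocol) and 70 patients per arm. Ignoring the hospital blocks, the SD of the arm difference in share is √(q(1−q) × 2/70).
- q = 0.2: SD 0.068; 95% limit 1.96 × 0.068 = 13 points; chance of a gap of 10 points or more, 14%.
- q = 0.4: SD 0.083; 95% limit 16 points; chance of a gap of 10 points or more, 23%.

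**2. What would such a gap do to the hazard ratio?** If heart failure carries R times the coronary hazard, a gap d with no treatment effect produces roughly [1+(R−1)(q+d/2)] / [1+(R−1)(q−d/2)]. At the 95% limit:

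| R | q = 0.2 | q = 0.4 |
|---|---|---|
| 2 | 1.12 | 1.12 |
| 3 | 1.21 | 1.20 |
| 4 | 1.28 | 1.25 |

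These are near-worst cases, and they occur in either direction.

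**3. Is the unstratified log-rank test valid?** In simulations of 140 patients (1,500 runs per scenario; R = 2 or 4; q = 0.2 or 0.4), rejection with no treatment effect was 4.2% to 5.5% unstratified and 4.3% to 6.1% stratified. Both are compatible with 5%. Only within trials selected for a gap of at least 10 points does the mean z of the unstratified test move, by about 0.3 at R = 2 and 0.5 to 0.6 at R = 3 to 4. Stratified, it stays near 0.

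**4. What power does stratification add?** There were two sets of simulations. Set A: hazard ratio 0.45, coronary rehospitalization 15% per year, censoring uniform over 0.5 to 2.08 years (the protocol's 6 to 25 months), 3,000 runs. Set B: hazard ratio 0.5, about 34 to 50 events, 1,500 runs. Neither removes the 30% dropout.

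| Set | R | q | Unstratified | Stratified | Gain (points) |
|---|---|---|---|---|---|
| A | 2 | 0.20 | 43.6% | 43.2% | −0.4 |
| A | 2 | 0.35 | 47.8% | 48.5% | 0.7 |
| A | 3 | 0.20 | 46.6% | 48.5% | 1.9 |
| A | 3 | 0.35 | 54.4% | 56.5% | 2.1 |
| A | 4 | 0.20 | 48.6% | 53.1% | 4.5 |
| A | 4 | 0.35 | 54.8% | 60.3% | 5.5 |
| B | 2 | 0.20 | 48.8% | 49.7% | 0.9 |
| B | 2 | 0.40 | 55.8% | 55.9% | 0.1 |
| B | 4 | 0.20 | 50.7% | 54.9% | 4.1 |
| B | 4 | 0.40 | 58.1% | 67.1% | 8.9 |

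**5. VO2 peak.** If covariates, including baseline, explain a share R² of the outcome variance (assumed), power with 49 per arm is Φ(3.605/√(1−R²) − 1.960).
- R² = 0: 95.0%
- R² = 0.1: 96.7%
- R² = 0.3: 99.1%
- R² = 0.5: 99.9%

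The whole gain over an unadjusted comparison is therefore 2 to 5 points. What disease category, age and gender add beyond baseline VO2 peak is only part of that.

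**6. If the second randomization did enforce balance.** Suppose allocations are redrawn until the standardized imbalance in the prognostic score is below a cut-off a. The variance of the unadjusted difference is then multiplied by 1 − R²(1−v), where v = 1 − 2aφ(a)/(2Φ(a)−1). The test still uses the unreduced standard error.
- a = 0.5: v = 0.081. At R² = 0.3 the factor is 0.724, and the type I error is 2[1−Φ(1.96/0.851)] = 2.1%. At R² = 0.5 it is 0.8%.
- a = 1.96: v = 0.759. The type I error is 4.2% at R² = 0.3 and 3.7% at R² = 0.5.

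Simulation with 98 completers agrees closely: 2.4% and 0.8% for the tight cut-off, 4.1% and 3.2% for the mild one. The adjusted test stayed near 5%. At R² = 0.3 under the tight cut-off, power was 97.4% unadjusted and 99.2% adjusted.

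**The case against.** The strongest reply has four parts.

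- **An unadjusted test in a randomized trial is valid.** This stands. A reader might infer that pooling the two diseases biases the result, or that chance imbalance invalidates it. The documents do not support that: over all randomizations imbalance adds variance, not bias. The z shifts in step 3 apply only to the 14% to 23% of trials picked out for being imbalanced, in either direction.
- **The protocol has its own remedy, the second randomization.** A reader might equally infer that imbalance must remain in the result. That overlooks this step, although the protocol does not explain how it would work once patients have started the programme, which is a separate matter. It does not rescue the unadjusted tests. If it does not operate, a realised imbalance is uncorrected; if it does, the tests become conservative (step 6). Both cases call for putting the factors in the analysis.
- **The clearest loss is on secondary endpoints.** This stands. For VO2 peak, a group-by-time test already cancels stable differences in level between coronary and heart-failure patients.
- **A condensed article may leave covariates to a fuller plan.** This stands in part. The point is confined to the tests the article fixes, and a Mann-Whitney test cannot take covariates, nor deliver the baseline adjustment the article promises for HeartQol, IPAQ and EQ-5D.

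**Conclusion.** The point holds as one of efficiency and consistency with the design, not of validity. Factors important enough to balance are absent from every test the article fixes. For rehospitalization, stratifying by disease category gains about nothing if heart failure doubles the hazard, and roughly 2 to 9 power points if it triples or quadruples it. Power stays at about 43% to 67% throughout, so this choice does not decide whether the trial can detect a rehospitalization effect. For VO2 peak the gain beyond baseline adjustment is small.

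The heart-failure share, hazard multiple, event rate, treatment hazard ratio and R² are all assumptions; the protocol gives none of them. The change is worth making because it costs little, corrects a realised imbalance, and keeps the type I error near its nominal level whether or not balance is enforced.

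**What to change.** In the Statistical analysis section:

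- **Rehospitalization endpoints:** prespecify a log-rank test stratified by disease category, with a Cox estimate stratified in the same way. Use mutually exclusive classes, any heart failure versus coronary disease without heart failure, because the eligibility wording allows a patient to have both. Keep further Cox covariates few, since events will be few.
- **VO2 peak and the other continuous endpoints:** replace the switch between Mann-Whitney and ANOVA with a baseline-adjusted model that includes disease category, age and gender. State that these terms are included whatever imbalance is observed, so that adjustment is not chosen after seeing the data.

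Cost: a few sentences, no extra patients and no new measurements. There is a small downside. The hazard ratio becomes conditional on stratum and any covariates, the rank-test branch gives way to a model whose assumptions need checking, and the two heart-failure categories are merged for stratification.

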## Discussion

The Telerehab III trial investigates the long-term effectiveness of the addition of a patient-tailored, internet-based telerehabilitation program implementing multiple CR core components and using both telemonitoring and telecoaching strategies to conventional CR.

Several clinical trials on cardiac telecare have recently been published, including the TIM-HF trial [16], the Telerehab II trial [9], the CHOICE trial [17–19], the COACH trial [20, 21], the eOCR trial [22, 23], and the TeleInterMed trial [24]. Hence two systematic reviews have recently been published regarding the feasibility, efficacy, safety and cost-effectiveness of cardiac telecare [7, 8].

The first review reported on cardiac telerehabilitation in CAD and CHF patients with a total of 13.248 patients enrolled in 37 studies; with a mean follow-up period of 9 months [7]. The review showed that telerehabilitation was associated with significantly favouring results for the tele-intervention regarding adherence to physical activity guidelines (Odds Ratio (OR) = 0,56, 95 % CI: 0,45-0,69); and the combined endpoint of adverse events and cardiovascular rehospitalizations (OR = 1,30, 95 % CI: 1,13-1,50). In the systematic review of Huang *et al.* nine trials of patients with CAD were reviewed. No statistically significant difference was found between telehealth interventions and center-based supervised CR in exercise capacity (standardized mean difference (SMD) = −0,01; 95 % CI: −0,12-0,10), body weight (SMD = −0,13; 95 % CI: −0,30-0,05), systolic and diastolic blood pressure (mean difference (MD) = −1,27; 95 % CI: −3,67-1,13 and MD = 1,00; 95 % CI: −0,42-2,43, respectively), blood lipid profile, smoking behaviour (risk ratio (RR) = 1,03; 95 % CI: 0,78-1,38), mortality (RR = 1,15; 95 % CI: 0,61-2,19), quality of life and psychosocial state.

Both reviews provide strong arguments for the non-inferiority and/or superiority of investigated telerehabilitation programs; when compared to standard center-based supervised CR. However, contrary to clinical trials included in these reviews, Telerehab III will be one of the first studies to prospectively test the long-term effectiveness of a patient-specific, multi core component cardiac telerehabilitation intervention; focusing both on telemonitoring and telecoaching. This comprehensive approach will have the ability to further improve effectiveness of tele-intervention based programs.

## Trial status

The study protocol and amendments were approved by the hospitals’ ethics committee prior to study start (B243201216043). The study is currently ongoing.

## Abbreviations

BMI: Body mass index
CABG: Coronary artery bypass grafting
CAD: Coronary artery disease
CEC: Clinical endpoint committee
CHF: Chronic heart failure
CPET: Cardiopulmonary exercise testing
CR: Cardiac rehabilitation
CVD: Cardiovascular disease
EF: Ejection Fraction
IPAQ: International physical activity questionnaire
NYHA: New York Heart Association
PCI: Percutaneous coronary intervention
RER: Respiratory exchange ratio
TTE: Transthoracic echocardiography
VF: Ventricular fibrillation
VT: Ventricular tachycardia
